#### Health economic analyses

We will compare the cost of DBT-6 vs DBT-12 from the perspective of the public healthcare payer. The output will be the incremental cost of DBT-6 compared to DBT-12. We will analyze the total cost as a dependent variable, using a regression model to estimate the difference in expected healthcare cost between the two groups. The intervention will be the primary independent variable and the regression model will adjust for potential confounding variables. In theory, an ordinary least squares model produces unbiased estimates even if the data are skewed; however, additional estimation methods (e.g., generalized linear models) and different uncertainty methods (e.g., parametric and non-parametric bootstrapping) will be explored to facilitate investigation of the impact of various cost assumptions [97–99].

Additionally, as a secondary economic analysis, we will explore the economic evaluation using the net benefit regression framework [100]. The outcome will be the incremental net benefit from DBT-6 for the intervention group compared to the standard DBT-12 group. We will also estimate the incremental cost per one self-injury episode avoided and the incremental cost per quality-adjusted life-year (QALY) gained, derived from the SF-36 and EQ-5D-5 L data. To estimate QALYs gained, we will convert SF-36 and EQ-5D-5 L data collected in the trial to utility scores using a validated algorithm [101–103]. The QALY is the gold standard measure of effectiveness recommended for economic evaluation and allows for a more global measure of the impact of a clinical intervention. Calculating QALYs requires the combination of health-related quality of life measures with data on health state duration. The EQ-5D-5 L has been used to evaluate the quality of life of patients with schizophrenia [104] and depression [105]; however, recently its validity in BPD studies has been questioned, so the SF-36 will be used for comparison in a sensitivity analysis. Statistical uncertainty will be characterized using a 95% confidence interval and a cost-effectiveness acceptability curve (CEAC) [106].

#### Attrition and treatment implementation

We will examine rates of treatment completion and attrition across both groups. We will conduct survival analyses to examine differences in the timing of treatment dropouts. In addition, we will compare rates of use of psychotropic medications and other adjunctive treatments at baseline and across both treatments. Treatment adherence ratings across both treatment arms will be evaluated. We also will examine potential site differences between the CAMH and SFU sites in terms of participant characteristics, and attrition. We will also examine potential therapist effects on treatment implementation and dropout rates.

#### Secondary analysis

##### Analyses of subtypes of BPD patients likely to benefit from DBT-6 versus DBT-12

Analyses related to predictors of treatment response will involve growth curve modeling, with covariates, with the two arms using both linear and over-dispersed Poisson hierarchical models. The effects of impulsivity and the rates of self-injury will be managed by person centering the variables. Growth curve models will be used to estimate the trajectories of the 4 diagnostic groups that are expected to moderate treatment response (PTSD, GAD, Cluster A, and Cluster C), but without the inclusion of covariates, provided they are not needed. Each diagnostic category will be estimated independently within a single model. The tests of both slopes and marginal effects will be carried out post-estimation, and will involve pair-wise multiple comparisons with alpha levels that are Holm’s Sequential Bonferroni adjusted.

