## Methods/design

### Study aims and hypotheses

#### Aim 1

To evaluate the clinical effectiveness of DBT-6 compared to DBT-12 for the treatment of chronically self-harming individuals with BPD. The following main hypotheses will be examined:

**Hypothesis 1a**: Patients in the DBT-6 arm will show equivalent reductions in the frequency and severity of self-harm across the treatment phase compared with patients in the DBT-12 arm. **Hypothesis 1b**: Patients in the DBT-6 arm will show equivalent reductions in the frequency and severity of self-harm across a 1-year post treatment follow-up phase, compared with patients in the DBT-12 arm.

#### Aim 2

To identify which subtypes of BPD patients are as likely to benefit from DBT-6 versus DBT-12.

**Hypothesis 2a:** Patients who present with high rates of self-harm and impulsive behaviours will have reductions in the frequency and severity of self-harm behaviours that are comparable in the DBT-6 arm and the DBT-12 arm, over the course of both the treatment phase and the 1-year post treatment follow-up.

**Hypothesis 2b**: Patients with co-occurring post-traumatic stress disorder, generalized anxiety disorder, or cluster A or C personality disorders will exhibit lesser reductions in the frequency and severity of self-harm behaviours in the DBT-6 arm compared to the DBT-12 arm, over the course of both the treatment phase and the 1-year post treatment follow-up. In other words, a subtype by duration interaction is expected.

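### Person-centring impulsivity and self-injury rate removes the between-patient differences that hypothesis 2a is about

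*Protocol article*

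**What the plan says.** Under Study aims and hypotheses (Aim 2), the protocol article states hypothesis 2a as: "Patients who present with high rates of self-harm and impulsive behaviours will have reductions in the frequency and severity of self-harm behaviours that are comparable" between the arms, over both the treatment phase and the one-year follow-up. Hypothesis 2b expects smaller reductions under DBT-6 in patients with PTSD, GAD, or cluster A or C personality disorder, and adds: "In other words, a subtype by duration interaction is expected".

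The Secondary analysis section plans growth curve models, linear and over-dispersed Poisson, that include both arms. On the two hypothesis 2a variables it says only: "The effects of impulsivity and the rates of self-injury will be managed by person centering the variables". It mentions covariates without listing them, and names neither a baseline term nor a person-mean term.

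For hypothesis 2b it says: "Growth curve models will be used to estimate the trajectories of the 4 diagnostic groups that are expected to moderate treatment response", and "Each diagnostic category will be estimated independently within a single model". The tests of slopes and marginal effects "will be carried out post-estimation, and will involve pair-wise multiple comparisons", with Holm adjustment. The pairs are not named.

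Table 1 schedules BIS-11 and SASII at baseline and every three months to month 24. Under Primary outcome, SASII is the primary outcome measure.

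**The concern.** Hypothesis 2a sorts patients by the level they bring to the trial: "Patients who present with high rates of self-harm and impulsive behaviours". The question is whether the arm difference changes as one moves from low-level to high-level patients. Person-centring expresses each value as a deviation from that patient's own average, so a patient with frequent self-harm and one with little both average zero.

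If the sentence is followed, the moderator analysis estimates something other than the hypothesis. A null result from a covariate stripped of between-patient information could then be read as confirming comparable benefit from six months in high-rate patients. The Background says that such findings may guide how patients are triaged, so the misreading would matter.

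For hypothesis 2b the question is smaller: whether the planned pair-wise comparisons are the interaction that the hypothesis names.

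**Working it through.** **1. The plan's own figure.** The Secondary analysis section gives none. The only computed size is 85 per group (Sample size and power analysis: margin 1.53, SD 4, α = 0.05, power 0.80, with the one-sided test named under Primary analyses). It reproduces: n = 2 × [4 × (1.645 + 0.842) / 1.53]² ≈ 84.5, so 85. This does not bear on the choice of model, but step 4 reuses the inputs.

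**2. What person-centring leaves.** Write patient i's value at visit t as x_it = b_i + w_it, where b_i is the stable level and w_it the fluctuation. The patient's mean is b_i + w̄_i, so the centred value is w_it − w̄_i, and b_i cancels.
- If x is a fixed baseline score, w_it = 0 and the centred value is exactly 0 for all 240 patients.
- If x is the repeated BIS-11 or SASII value, only within-patient fluctuation remains. The mean being subtracted covers visits after randomisation, which treatment length may have changed.
- If x is the repeated self-injury rate, the covariate is a centred copy of the outcome, which then stands on both sides of the model.

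**3. Size of the loss for hypothesis 2a.** In 500 simulated trials (240 patients, 9 visits, time scaled 0 to 1), the assumed arm × trait × time effect was 0.50, the trait SD 1 and the within-patient SD 0.7. Mean estimates, with the SD across trials:
- person-centred covariate: 0.002 (0.33)
- patient's true stable level: 0.502 (0.16)
- single baseline score: 0.335 (0.13)

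The last figure is the expected attenuation: 1 / (1 + 0.7²) = 0.671, and 0.50 × 0.671 = 0.336. The simulated outcome was continuous. The cancellation in step 2 does not depend on the outcome distribution.

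**4. Hypothesis 2b: which pairs?** In 3,000 simulated trials per scenario there were 85 patients per arm, SD 4, two diagnoses that may co-occur, and two-sided 0.05 without Holm adjustment. Prevalences of 20%, 40% and 50% are assumptions.
- With no interaction and a uniform arm effect of 1.53, the arm contrast within a diagnosis was significant in 21%, 35% and 40% of trials. The interaction contrast stayed at about 5%.
- With an interaction of 1.53, diagnosis against diagnosis with arms pooled was significant in 11 to 13%, against about 17 to 24% for the interaction contrast.
- The analytic check agrees. SE = 4 × √(2/85) × √(1/f + 1/(1−f)), which is 1.534 at f = 0.2 and 1.227 at f = 0.5. Power Φ(1.53/SE − 1.96) is then 0.17 and 0.24.

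**The case against.** The article condenses a fuller protocol, and an analysis plan may exist. Person-centring is normally paired with the person mean, and the unlisted covariates might include it. This stands only in part. The article does not leave the handling open; it names one method, and that method alone cannot estimate hypothesis 2a. Adding person means back would restore differences between patients, but those means would include post-randomisation values, and for self-injury they would be averages of the outcome. Only a baseline measure matches what patients present with.

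It is also fair that person-centring is meant for time-varying variables, so the exact-zero result describes one reading. The other reading, repeated values, is covered in step 2 and does no better.

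On hypothesis 2b the objection largely succeeds. A reader might infer that pair-wise tests cannot address the interaction, or that every arm-by-diagnosis cell will be compared with every other. The text supports neither. It calls the diagnoses moderators, includes both arms, estimates each category within one model and tests slopes and marginal effects. Comparing the arm difference between patients with and without a diagnosis is a pair-wise comparison and is also the interaction contrast. An arm contrast within a diagnosis also answers the first sentence of hypothesis 2b, although it does not establish moderation. Leaving the pairs unnamed is detail that an article may defer.

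**Conclusion.** The point holds for hypothesis 2a: the stated handling removes the between-patient information that the hypothesis needs. The algebra is exact. The fall from 0.50 to 0.00 illustrates it under assumed effect and noise values.

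For hypothesis 2b only a clarification is supported. The document states that "a subtype by duration interaction is expected" and does not exclude testing it, but it does not name that contrast. Two plausible readings of the planned comparisons would not test it by themselves. The 21 to 40% figure rests on assumed prevalences and an assumed uniform arm effect of 1.53.

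A reader might conclude that Aim 2 as a whole cannot be answered. That does not follow, because hypothesis 2b does not depend on person-centring. The primary non-inferiority comparison is not touched.

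**What to change.** **Hypothesis 2a.** Replace the person-centring sentence with:
- baseline BIS-11 and the baseline SASII count (suitably transformed), each grand-mean centred and interacted with arm and time;
- only post-baseline self-injury as the outcome in this analysis, so that the baseline SASII count is not both moderator and first outcome point;
- the arm difference with its confidence interval at stated high baseline values, over both the treatment and follow-up phases. If a limit is to define comparable, state it for this purpose, since 1.53 was set for the whole-sample comparison.

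**Hypothesis 2b.** State that the four diagnoses enter as non-exclusive yes/no indicators, and that Holm is applied to the four arm-by-diagnosis(-by-time) interaction contrasts. Arm differences within a diagnosis can still be reported as description.

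**Cost.** Wording only; the baseline data are already collected. There are two small downsides. A single baseline score is a noisy measure of the stable trait and attenuates the moderation estimate (0.34 against 0.50 under the assumptions above). Interaction precision will also be low: for hypothesis 2b, power of about 17 to 24% for an interaction of 1.53 before Holm adjustment. Report intervals, and do not read a non-significant interaction as evidence of comparable benefit.

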### Sample size and power analysis

The study was designed to test whether DBT-6 is not inferior to DBT-12 (an established treatment). The estimate of the sample size required for a non-inferiority test was based on the effect sizes from prior DBT RCTs [30, 62]. Post-treatment suicide and self-harm estimates over 4 months were 2.26 episodes for DBT-6 and 0.73 for DBT-12 (SD_pooled_ = 4). We expected no significant differences between the DBT-6 and DBT-12 conditions in terms of reductions in the frequency and severity of self-injury episodes at 1 year. We therefore defined our delta, the clinically significant range of indifference for our non-inferiority trial, as a difference in outcomes of 1.53 (SD = .04) episodes in the frequency of self-harm episodes at post-treatment. To achieve this maximum of 1.53 or less in the difference of self-injury rates with adequate power (α = .05; 1 - β = .80), 85 participants per group are required to show non-inferiority of treatment. Allowing for a 30% dropout rate, we will recruit 120 participants per group. The sample size calculation also addresses the necessary power for secondary analyses, given that the sample size required for null hypothesis significance testing is typically less than those required for non-inferiority [89].

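### Aim 2 and hypothesis 2a claim that subtypes do as well on DBT-6 as on DBT-12, but the only inferential method stated for the subtype analyses is difference testing, which cannot establish that

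*Protocol article*

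**What the plan says.** Under Study aims and hypotheses, Aim 2 reads "To identify which subtypes of BPD patients are as likely to benefit from DBT-6 versus DBT-12". Hypothesis 2a concerns patients who self-harm often and are highly impulsive. Its prediction, for the treatment period and the year after it, is that they "will have reductions in the frequency and severity of self-harm behaviours that are comparable in the DBT-6 arm and the DBT-12 arm". Hypothesis 2b points the other way: patients with PTSD, GAD or a cluster A or C personality disorder should improve less on DBT-6, and "In other words, a subtype by duration interaction is expected".

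The Secondary analysis section plans growth curve models. One sentence deals with impulsivity and self-injury rate by centring. The next sentences concern "the 4 diagnostic groups that are expected to moderate treatment response (PTSD, GAD, Cluster A, and Cluster C"). The section ends by saying that post-estimation tests of slopes and marginal effects "will involve pair-wise multiple comparisons with alpha levels that are Holm’s Sequential Bonferroni adjusted". It gives no margin and no confidence-bound criterion.

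The Primary analyses section specifies non-inferiority tests for the primary hypotheses. Sample size and power analysis sets the 1.53-episode margin for the overall post-treatment comparison. It defends the power of the secondary analyses on the ground that "the sample size required for null hypothesis significance testing is typically less than those required for non-inferiority".

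**The concern.** A test of no difference can support 2b by rejecting. It cannot support 2a, because failing to reject is what one expects from a small subgroup whether or not the arms differ. The trial treats its primary sameness question properly, with a margin and a one-sided test, but carries neither over to the secondary one.

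Aim 2 is meant to inform triage: the Background says that clarifying which subsets do well with which length will affect resource allocation and how patients are triaged. If comparability were inferred from a non-significant comparison, a subtype in which DBT-6 is worse by the full margin could be labelled suitable for the shorter course. For 2a, those are the patients who self-harm most.

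**Working it through.** **Inputs from Sample size and power analysis.** Margin 2.26 − 0.73 = 1.53 episodes; pooled SD 4; alpha .05; power 80%; 85 per group; 120 recruited per group to allow for 30% dropout. The one-sided form of the primary test comes from Primary analyses. The .04 printed beside the margin cannot be the SD used, since it would give n = 1 per group.

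**Reproducing the stated figure.** n per group = 2 × (1.645 + 0.842)² × 4² / 1.53² = 84.5, rounded up to 85. This matches.

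**Assumptions.** Subtype size is not given, so I show a range, with equal numbers in both arms:
- 120 × 0.70 = 84 per arm: the whole sample after dropout
- 120 / 2 = 60 per arm: half the sample, no loss
- 84 / 2 = 42 per arm: half, after dropout
- 84 / 4 = 21 per arm: a quarter, after dropout

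**Chance of missing a margin-sized harm.** The true DBT-6 minus DBT-12 difference is 1.53 and SD is 4, so d = 1.53 / 4 = 0.3825. The miss rate is 1 minus the power of a two-sided two-sample t-test. The last column is the first Holm step for an assumed family of four, .05 / 4 = .0125. It matters for 2a only if Holm applies there.

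| Per arm in subtype | Miss rate at .05 | Miss rate at .0125 |
|---|---|---|
| 84 | 31% | 52% |
| 60 | 45% | 67% |
| 42 | 59% | 78% |
| 21 | 77% | 90% |

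Hand check at 42 per arm: SE = 4 × √(2/42) = 0.873; 1.53 / 0.873 = 1.753; the normal approximation gives Φ(1.753 − 1.960) = 0.42, a miss rate of 58%.

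**The sample-size reassurance.** For a difference of 1.53, a two-sided .05 test with 80% power needs 2 × (1.960 + 0.842)² × 16 / 1.53² = 107.3, so 108 per group, against 85 for the one-sided non-inferiority test. On the trial's own inputs, significance testing for an effect of that size does not need fewer patients.

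**What a bound-based rule would achieve.** With a true difference of zero, the chance that the one-sided 95% upper limit falls below 1.53 is Φ(1.53 / (4√(2/n)) − 1.645):
- n = 42: Φ(1.753 − 1.645) = 54%
- n = 60: Φ(2.095 − 1.645) = 67%

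**The case against.** - **Reading of non-significance.** A reader might infer that the plan counts 2a as confirmed when p exceeds the threshold. The article never says so, and this part of the objection stands. It does not remove the gap, because no other stated rule could support 2a.
- **Null value.** The section does not state the null value, so a test of marginal effects need not be a difference test. But the article names non-inferiority only for the primary hypotheses and describes the secondary analyses as significance testing. That remark concerns sample size and is not a decision rule, so it supports this reading without settling it.
- **Holm and 2a.** A reader might also infer that Holm adjustment makes a comparable verdict easier for 2a, since it lowers alpha. The Holm sentence follows the text on the four diagnostic groups and may cover only 2b. The .0125 column is therefore conditional. If Holm covers only 2b, the article states no inferential method suited to 2a.
- **Size.** It is tempting to say that a margin-sized harm would be missed in most cases. The documents do not support that in general: at .05 the miss rate is 45% with 60 per arm and 31% with 84. Intention-to-treat analysis may also retain treatment dropouts, and the planned repeated-measures models with continuous or count moderators could have different precision from a split-sample t-test.
- **Detail left to an analysis plan.** A condensed article may leave a secondary decision rule to the full plan. Here it does more than omit one: it states a type of test and a testing framework, and neither fits a sameness claim.

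**Conclusion.** The point holds in conditional form. The stated method fits 2b and cannot establish 2a or any statement that a subtype is as likely to benefit from DBT-6. If non-significance were taken as comparability, a 1.53-episode excess on DBT-6 would go undetected in 31% to 77% of trials for subtypes of 84 down to 21 per arm at .05, and more often if Holm also applies.

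These figures rest on SD 4, a single-time-point comparison of two means, and assumed subtype sizes. SD 4 and the 1.53 margin were set for the whole sample from 4-month estimates; neither can be presumed to hold in a subtype selected for high self-harm. The mismatch between claim and test does not depend on these figures. It concerns a named secondary aim and should be corrected, but it does not affect the primary non-inferiority test.

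**What to change.** **Post-treatment frequency.** For 2a and any statement that a subtype is as likely to benefit, report the model-based DBT-6 minus DBT-12 difference in self-harm frequency at the high level of the baseline moderator, or in the subtype, with its one-sided 95% upper limit. Claim comparability only if that limit is below a margin prespecified for that outcome and time window; otherwise report the result as inconclusive. The primary margin can serve here once it is put on the 3-month SASII interval. Assuming a constant rate, that is 1.53 × 3/4 = 1.15 episodes. The authors should confirm that it is acceptable in a high-self-harm subtype.

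**Severity and 1-year follow-up.** The article sets no margin for these. Report estimates with confidence intervals and make no comparability claim.

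**Holm.** Keep it for the 2b interaction tests only, and say so.

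**Cost.** Wording only, with no new data. The claim becomes harder to make: with the 1.53 margin, SD 4 and no true difference, the bound is met about 54% of the time at 42 per arm and 67% at 60. These figures use the unscaled margin and SD; the SD for a 3-month interval is not given. Some subtypes will be inconclusive, which reflects what subgroups of this size can show.

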### Data safety monitoring

A data safety monitoring committee (DSMC) was established and composed of three independent researchers specializing in BPD and self-harm, cognitive behavior therapy, and biostatistics. The DSMC is responsible for monitoring the research protocol, reviewing data, assessing the safety of the trial, reporting adverse events, reviewing unanticipated problems, and monitoring protocol violations in accordance with the policies and procedures outlined in the institutional research ethics boards (REBs) at each site and in accordance with Canadian Institutes of Health Research’s (CIHR) policies and procedures concerning data and safety monitoring. The DSMC will communicate any new information to the REB at both sites over the course of the trial, and the site supervisors ([name]), in consultation with the research team will make the decision whether to continue, suspend, modify or stop the trial, or amend the protocol. The site supervisors ([name]) are responsible for monitoring and reporting serious adverse events to the DSMC. Serious adverse events are defined as any untoward medical occurrence that results in death, is life-threatening, results in persistent or significant disability/incapacity, results in a congenital anomaly/birth defect, or any important medical event that may jeopardize the health of the research participant or may require medical intervention to prevent one of the outcomes listed above. Serious adverse events involving self-harm behaviour was operationalized as very high to severe medical risk according to the SASII lethality scale.

